## Abstract

**Background:**

Percutaneous vertebroplasty (PVP) often causes moderate-to-severe intraoperative pain, with current local anesthesia methods providing limited relief. The erector spinae plane block (ESPB) has shown promise in regional analgesia but lacks evidence for PVP. This study aims to test the hypothesis that a preoperative bilateral ESPB provides superior intraoperative analgesia compared to local anesthetic infiltration alone in patients undergoing lumbar PVP. The primary objective is to compare the incidence of moderate-to-severe pain between the two groups.

**Methods:**

This single-center, randomized, single-blind, parallel-group trial will enroll 66 patients undergoing lumbar PVP, who will be randomized to ESPB (20 mL 0.25% ropivacaine bilaterally) or local anesthesia (1% lidocaine). Primary outcome: incidence of moderate-to-severe pain (VAS > 3). Secondary outcomes will include maximum pain scores, patient/surgeon satisfaction, rescue analgesia, time to first mobilization, incidence of adverse events, anesthesia preparation time, and total operating-room occupancy time.

**Discussion:**

The study aims to validate ESPB’s efficacy in PVP, potentially reducing opioid use and improving recovery. Strengths include CONSORT adherence and pragmatic outcomes, though single-center design and limited follow-up may affect generalizability.

**Conclusion:**

This trial will determine whether ESPB offers superior analgesia for PVP, guiding future pain management strategies. If proven effective, ESPB could be adopted as a key component of multimodal analgesia for vertebral augmentation, potentially leading to reduced opioid dependence, improved patient comfort, and faster recovery. The results will guide future evidence-based pain management strategies for these common procedures.

## Introduction

Percutaneous vertebroplasty (PVP) is a minimally invasive surgical procedure widely utilized in the treatment of osteoporotic vertebral compression fractures and vertebral tumors (Haibier et al., 2023). While offering advantages such as minimal invasiveness and rapid recovery, moderate-to-severe pain is frequently experienced by patients during the procedure, often attributed to cement injection and vertebral body expansion (Liu et al., 2024; Della Puppa, Andreula & Frass, 2008). Currently, local anesthesia, such as lidocaine infiltration, is commonly employed during PVP; however, its analgesic efficacy is often limited and may not adequately cover the pain induced by surgical stimulation, particularly the intense pain associated with cement injection (Liu et al., 2024; Della Puppa, Andreula & Frass, 2008). Consequently, the optimization of intraoperative analgesia strategies to enhance patient comfort represents a critical clinical challenge.

In recent years, regional anesthesia techniques have gained increasing prominence in perioperative pain management, with the erector spinae plane block (ESPB) attracting attention due to its ease of performance, favorable safety profile, and effective coverage of the trunk’s nerve supply (Kot et al., 2019; Oostvogels et al., 2024). ESPB involves the injection of local anesthetic either deep or superficial to the erector spinae muscle, leading to the blockade of the dorsal rami and a portion of the ventral rami of spinal nerves, thereby achieving analgesia in the thoracolumbar region (Viderman, Aubakirova & Abdildin, 2022; Liu et al., 2023). Although the analgesic effectiveness of ESPB has been validated in several trials for lumbar spinal fusion, research on its application in PVP remains relatively scarce (Lu et al., 2025; Sharma et al., 2024; Zhang et al., 2021).

Based on its documented mechanism of action, we hypothesize that ESPB can provide effective analgesia for PVP. The cranio-caudal spread of local anesthetic within the fascial plane is known to block the dorsal rami of spinal nerves (which innervate the vertebral periosteum and posterior ligaments) and may also affect the ventral rami *via* paravertebral space diffusion (Coppens, Eochagain & Dewinter, 2023; Bagnoli et al., 2024; Schwartzmann et al., 2018). It is thus postulated that this broader neural blockade can cover the primary nociceptive sources activated during PVP, such as pedicle needle insertion and vertebral body distension.

The present study aims to investigate the analgesic efficacy of ESPB in lumbar PVP, with further analysis of its safety and feasibility. It is anticipated that the findings of this study will offer a novel and optimized approach to anesthetic management in lumbar PVP, ultimately improving the patient’s surgical experience.

## Methods

### Study objective

Explore the analgesic effect of ESPB in lumbar PVP.

### Study design

Single-center, randomized, single-blind, parallel-group, following the CONSORT guidelines and the Declaration of Helsinki.

### Ethical considerations

This study has been approved by the Medical Ethics Committee of the First Affiliated Hospital of Henan University of Chinese Medicine (Ethics Approval Number: 2025HL-446-01), and has been registered in the Chinese Clinical Trial Registry (Registration Number: ChiCTR2500107309). The study protocol followes the CONSORT guidelines and the Declaration of Helsinki. All subjects will sign written informed consent and will have the right to withdraw from the study at any time. All collected data will be anonymized.

### Participants

Inclusion criteria are: Age 18 years or older, American Society of Anesthesiologists (ASA) physical status classification of 2 or 3, elective lumbar PVP involving a single vertebral level.

Exclusion criteria are: Pregnancy, allergy to local anesthetics, coagulopathy, PVP performed under general anesthesia, preoperative use of analgesic medications, history of chronic pain, psychiatric or neurological disorders, refusal to participate in the study.

### Recruitment

Prospective subjects will be recruited from the Department of Orthopedics at the First Affiliated Hospital of Henan University of Chinese Medicine. All patients scheduled to undergo single-segment PVP under local anesthesia will be screened for eligibility. Eligible patients will be provided with a detailed explanation of the research protocol, including potential benefits and risks, and all questions regarding the study will be addressed. Written informed consent will be obtained from all patients prior to enrollment. It is anticipated that participant recruitment will commence in September 2025. Based on the current surgical volume at our institution, we anticipate that the recruitment phase will last for approximately 4 months, with the entire study (including follow-up and data analysis) expected to be completed by the end of January 2026. The flow of participants through the study will be summarized using a CONSORT diagram, as presented in Fig. 1.

**Figure 1 fig-1:**
[figure not shown]
CONSORT flow diagram.

### Randomization

Random numbers will be generated by an independent researcher using the RAND function in Excel, and patients will be divided into local anesthesia group (LA group) and ESPB group in a 1:1 ratio. The random results will be sequentially stored in opaque envelopes, kept by the research coordinator.

### Blinding

Since the LA group requires the surgeon to perform local infiltration anesthesia, it will be impossible to blind the surgeons. Patients, the anesthesiologists responsible for perioperative management, outcome assessors, and statistical analysts will be blinded to group assignment.

A research coordinator will be designated to maintain and distribute randomization numbers and coordinate communication between researchers. After the patient enters the room, the research coordinator will open the envelope and inform an independent anesthesiologist of the patient’s group assignment. This anesthesiologist will leave after the patient’s intervention is completed and will not participate in subsequent research. Another anesthesiologist will be responsible for the patient’s perioperative management. A researcher blinded to group assignment will be responsible for postoperative follow-up.

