### Interventions

LA group: Patients will be placed in a prone position. The surgeon will disinfect, drape, and after localization, will use 1% lidocaine for local infiltration anesthesia.

ESPB group: Patients will be placed in a lateral decubitus position. This position is standard for performing a bilateral lumbar ESPB as it provides optimal ergonomics for the operator, facilitates ultrasound probe placement, and allows for stable needle access to the transverse processes on both sides. An independent nerve block specialist (with over 3 years of experience in ultrasound-guided nerve blocks) will perform a bilateral ESPB in the operating room. The block will be performed at the vertebral level corresponding to the planned surgical level (*i.e*., the level of the vertebral fracture). A curvilinear probe (2–5 Hz) will be selected, and a parasagittal approach (approximately 3 cm lateral to the posterior midline) will be used for localization. The transverse process of the target vertebral level will be located, and a 24 G needle will be inserted in-plane to the surface of the transverse process. After negative aspiration for blood and cerebrospinal fluid, 3 mL of normal saline will be injected to separate the erector spinae muscle from the transverse process to confirm correct placement. A total of 20 mL of 0.25% ropivacaine will be administered at this level to achieve cranio-caudal spread of local anesthetic within the fascial plane. The same procedure will be performed on the contralateral side.

Concurrently, during the performance of the nerve block, the surgical team will use this time to prepare the sterile instruments and mix the polymethylmethacrylate bone cement. Upon completion of the bilateral blocks, the patient will be promptly assisted into the prone position. The surgical field will then be disinfected and draped in the standard fashion. A standardized minimum block-to-incision interval of 20 min will be maintained between the completion of the block and the surgical skin incision to allow for adequate sensory blockade onset.

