### Adverse event monitoring

Adverse events (AEs) will be systematically monitored from the initiation of the anesthesia intervention until patient discharge. AEs of specific interest include local anesthetic systemic toxicity (LAST), pneumothorax, block failure, nerve injury, significant hemorrhage at the block site, and infection.

AEs will be defined according to standard clinical criteria. LAST will be defined as the acute onset of neurological (*e.g*., metallic taste, perioral numbness, seizures, loss of consciousness) or cardiovascular (*e.g*., arrhythmia, hypotension) symptoms following local anesthetic injection (Van Wicklin, 2025). Pneumothorax will be suspected in the presence of acute-onset pleuritic chest pain, dyspnea, oxygen desaturation, or diminished breath sounds on auscultation, and confirmed by chest X-ray (Harnedy, Foley & Fitzgerald, 2025). Block failure will be defined as the inability to achieve a detectable sensory deficit in the surgical dermatomes *via* pinprick test 20 min after ropivacaine injection. All AEs will be assessed and documented by the attending anesthesiologist and the surgical team.

Management protocol: LAST: In the event of suspected LAST, the “Stop, Call, Lipid” protocol will be initiated immediately: (1) Stop injection of local anesthetic; (2) Call for help; (3) Administer a 20% lipid emulsion bolus (1.5 mL/kg) intravenously over 2–3 min, followed by a continuous infusion (0.25 mL/kg/min). Advanced Cardiac Life Support protocols will be followed, with adjustments (*e.g*., reduced epinephrine dose) as per LAST treatment guidelines (Van Wicklin, 2025). Pneumothorax: For a suspected pneumothorax, supplemental oxygen will be administered immediately. A chest X-ray will be obtained for confirmation. A consulting cardiothoracic surgeon will be notified. For a large or symptomatic pneumothorax, needle decompression followed by chest tube insertion will be performed (Harnedy, Foley & Fitzgerald, 2025). Other AEs: Significant hemorrhage or neurological deficits will be promptly investigated with ultrasound or other appropriate imaging (*e.g*., MRI) and managed in consultation with relevant specialists (*e.g*., neurologists, vascular surgeons).

All AEs, regardless of their relation to the study intervention, will be recorded in the Case Report Form (CRF). Serious AEs will be reported to the Principal Investigator and the Medical Ethics Committee within 24 h.

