### Data collection

Following the provision of written informed consent by the patients, baseline data will be collected. To standardize the procedural timeline and assess the impact of the interventions on workflow, the following time points will be recorded for all patients: the time of entering the operating room (T1), the time of completion of the nerve block or local anesthesia infiltration (T2), the time of surgical skin incision (T3), and the time of leaving the operating room (T4). The ‘anesthesia preparation time’ will be defined as the interval from entering the operating room (T1) to the completion of anesthesia intervention (T2). The ‘total operating-room occupancy time’ will be defined as the interval from entering (T1) to leaving (T4) the operating room. The ‘block-to-incision’ interval (T2 to T3) will also be calculated. The anesthesiologist responsible for the patient’s perioperative management, who is blinded to group assignment, will assess and record the patient’s VAS pain score at three specific timepoints: (1) during trocar insertion into the pedicle, (2) during polymethylmethacrylate bone cement injection, and (3) at the end of the procedure before transferring the patient out of the operating room. The intraoperative incidence of moderate-to-severe pain will be recorded. Postoperatively, the highest intraoperative pain score, patient satisfaction with intraoperative analgesia, and surgeon satisfaction will be obtained. The incidence of rescue analgesia within the first 24 h post-surgery, as well as the time to first mobilization, will be collected by an independent researcher. The incidence of adverse events will be recorded from the initiation of the intervention until patient discharge.

All data will be initially recorded on paper-based CRF. These data will then be entered into an Excel database, with verification performed by two independent individuals. Although an independent data monitoring committee was not established for this single-center trial, data accuracy and protocol adherence will be safeguarded through internal quality control processes under the supervision of the principal investigator and the institutional ethics committee.

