### Limitations

First, conducting the trial at one tertiary hospital may limit generalizability to different surgical teams, patient demographics and institutional protocols. Furthermore, as all ESPB procedures will be performed by a single, experienced operator to ensure consistency, the results may not be fully generalizable to clinical settings where practitioners have varying levels of expertise in ultrasound-guided regional anesthesia. Second, while patients, outcome assessors and data analysts are blinded, surgeons cannot be masked to group allocation, introducing a possibility of performance bias in intra-operative conduct. Third, only ASA II–III adults undergoing single-level lumbar PVP are eligible. Results may not extrapolate to multilevel PVP, thoracic procedures, general-anesthesia cases or patients with severe systemic disease. Fourth, all ESPB procedures in this trial will be performed by a single, experienced nerve block specialist to ensure consistency and technical quality. While this minimizes internal performance variability, it may limit the generalizability of our results to settings where operators have different levels of expertise with ultrasound-guided regional anesthesia. Future implementation of this technique would benefit from standardized training protocols to ensure reproducible efficacy. Fifth, the use of local infiltration as the control intervention, instead of a sham (saline) ESPB, means that our design cannot fully isolate the specific “block effect” from potential non-specific effects or the profound difference in procedural experience between the groups. This was a deliberate choice informed by ethical considerations and our goal to conduct a pragmatic trial comparing two distinct clinical strategies. Finally, outcomes are monitored up to 24 h post-procedure; the study will not capture delayed complications (*e.g*., rebound pain, cement leakage-related irritation) or long-term outcomes such as the development of persistent pain or chronic opioid use.

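### Patients are listed as blinded, but the two procedures tell an awake patient which arm they are in, so the primary VAS outcome is reported without patient blinding; the VAS recorder's blinding is not shown to be protected

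*Protocol article*

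**What the plan says.** The Study design section labels the trial "Single-center, randomized, single-blind, parallel-group, following the CONSORT guidelines and the Declaration of Helsinki". The Blinding section excludes only the surgeons from blinding and then says: "Patients, the anesthesiologists responsible for perioperative management, outcome assessors, and statistical analysts will be blinded to group assignment". Its one described safeguard is that the anesthesiologist told of the allocation departs once the assigned procedure has been given, and a second anesthesiologist manages the case. Under Data collection, this managing anesthesiologist, "who is blinded to group assignment, will assess and record the" VAS at trocar insertion, cement injection and the end of the procedure. The primary outcome is the proportion of patients who report a VAS above 3 at any of these three points.

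The Interventions section gives the arms different procedures. For the control arm: "LA group: Patients will be placed in a prone position" and "The surgeon will disinfect, drape, and after localization, will use 1% lidocaine for local infiltration anesthesia". For the other arm: "ESPB group: Patients will be placed in a lateral decubitus position". A nerve block specialist then blocks both sides under ultrasound, the patient is turned prone, and at least 20 min must pass between the end of the block and incision. Perioperative management rules out premedication and sedation in both arms.

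The Limitations section again lists patients and outcome assessors as blinded. It also says that there is no sham block and acknowledges "the profound difference in procedural experience between the groups".

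**The concern.** A patient who has heard both arms described at consent, is fully awake, and is either needled on both sides under ultrasound while lying lateral or infiltrated by the surgeon while prone can tell which treatment was given. The primary outcome is that patient's own rating, cut at 3. Expectation can therefore move the result directly, whatever is done to blind the person writing the score down. The same score triggers intraoperative sufentanil, so part of the opioid-consumption outcome depends on it. Patient satisfaction shares the problem, and surgeon satisfaction is scored by someone the plan already says is unblinded.

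At stake is what readers will be told. If the blinding statement passes into the trial report, the primary outcome will be presented as protected against patient expectation when it is not. The weaker second question is whether the VAS recorder is really kept unaware of the arm.

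**Working it through.** **1. The plan's own figure.** Sample size inputs: 70% against 35%, two-sided α = 0.05, power 0.80, 1:1. With pooled variance under the null, the mean rate is (0.70 + 0.35)/2 = 0.525 and

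n = [1.960 × √(2 × 0.525 × 0.475) + 0.842 × √(0.70 × 0.30 + 0.35 × 0.65)]² / 0.35² = [1.384 + 0.557]² / 0.1225 ≈ 30.8, so 31 per group and 62 in total.

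With 5% dropout, 31/0.95 = 32.6, so 33 per group and 66 in total. The stated size reproduces and does not bear on blinding.

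**2. Can the patient be unaware of the arm?**

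| Feature | LA arm | ESPB arm | Section |
|---|---|---|---|
| Starting position | Prone | Lateral, then turned prone | Interventions |
| Who gives the anesthetic | Surgeon, after draping and localization | Separate block operator, before prone positioning and draping | Interventions |
| Technique | Infiltration | Ultrasound-guided needle on each side | Interventions |
| Interval to incision | None fixed | At least 20 min from the end of the block | Interventions |
| Sedation | None | None | Perioperative management |
| Sham | None | Not applicable | Limitations |
| Told about the protocol | Yes | Yes | Recruitment |

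No section describes anything that would hide these differences from the patient.

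**3. Can the VAS recorder be unaware of the arm?** The handover comes when the assigned procedure is finished. In the ESPB arm the patient is then still to be turned and draped. In the LA arm the patient is already prone and draped. A person who takes over at that moment could infer the arm. Block failure is defined by a pinprick test 20 min after ropivacaine, which applies only to the ESPB arm and, on a plain reading, falls after the block operator has gone. On documentation: "All AEs will be assessed and documented by the attending anesthesiologist and the surgical team". Against this, no entry time is given for the recorder, and the attending anesthesiologist is not expressly identified as the recorder. The finding here is that protection is not shown.

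**4. How much could reporting bias matter?** The shifts are assumptions; nothing in the documents gives their size. Let a and b be the numbers with VAS above 3 in the LA and ESPB arms, 33 each. The uncorrected chi-square is

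X² = 66(a − b)² / [(a + b)(66 − a − b)], significant when above 3.84.

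For example, a = 23 and b = 15 gives 66 × 64 / (38 × 28) = 3.97, which is significant; b = 16 gives 66 × 49 / (39 × 27) = 3.07, which is not.

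With no true effect, a 70% rate in both arms, and knowledge of the arm lowering reported VAS above 3 by s in the ESPB arm only, the chance of significance is the sum of Bin(a; 33, 0.70) × Bin(b; 33, 0.70 − s) over all significant pairs (a, b):

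| Assumed shift s (points) | Chi-square | Fisher |
|---|---|---|
| 0 | 5.3% | 2.5% |
| 5 | 7.6% | 4.1% |
| 10 | 14.5% | 9.1% |
| 15 | 26.1% | 18.2% |
| 20 | 41.3% | 31.6% |

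**The case against.** The strongest defence is that the plan is partly candid. Its fifth limitation says that, without a sham, the block effect cannot be fully separated from non-specific effects or from the differing procedural experience, and it presents this as a deliberate pragmatic choice. This stands: the choice of comparator is defensible, and it would be wrong to say that only surgeon performance bias is conceded. But the same section still counts patients as blinded and does not name reporting bias in the primary outcome, so the disclosure does not remove the contradiction.

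Second, a condensed article may leave the recorder's entry time to the full protocol, and a second anesthesiologist is a real safeguard. This also stands. A reader might infer that the recorder certainly learns the arm; the documents support only doubt.

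Third, a reader might call the whole trial open-label. The documents do not support that. Nothing contradicts the blinding of the analysts, or of the follow-up researcher who collects postoperative outcomes.

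Finally, the calculation rests on assumed shifts. It shows sensitivity to bias and does not predict a false positive.

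**Conclusion.** The statement that patients are blinded is wrong as written and must be corrected. This rests on the plan's own account of the procedures, the absence of sedation, the consent explanation and the missing sham, and it needs no numerical assumption. The affected outcomes are the primary VAS outcome and patient satisfaction, with intraoperative rescue opioid use affected through the VAS trigger.

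On the recorder, the conclusion is limited: blinding is asserted, the text does not show how it is maintained, and the handover point and the ESPB-only pinprick test give reason for doubt.

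The possible size depends on the assumed reporting shift. With no true effect, a shift of 10 to 20 points would make a nominal 5% test significant in roughly 15% to 41% of trials by chi-square, or 9% to 32% by Fisher's test. Smaller shifts matter less.

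**What to change.** 1. **Wording.** Remove patients from the blinded lists in Blinding and Limitations. Reconcile the single-blind label in the Abstract, Study design and Discussion by naming who is blinded. State in Limitations that the primary VAS and the satisfaction scores come from unblinded patients or surgeons and may carry expectation bias.

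2. **Recorder.** In both arms, have the VAS-recording anesthesiologist enter only after skin incision (T3). The independent anesthesiologist already in the plan covers until then, and does and documents the pinprick test. Amend the Blinding sentence on when that person leaves, and the Adverse event monitoring sentence on who documents events, so that they agree. This protects the recorder; it cannot protect the patient's own rating, for which item 1 is the remedy.

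3. **Optional check.** Record the VAS recorder's guess of the arm, noting that a guess at the end of the case may reflect observed pain relief and not a failure of blinding.

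The cost is a less favourable stated blinding status and a later handover by staff already assigned. Sample size, arms and endpoints are unchanged.
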